#### 2.2.3. Sample Size

To calculate the sample size, we will use the data obtained in the study of Dalbosco-Salas et al. [34] because the intervention is similar to ours, and it is developed in PHC, despite being a clinical trial. To the best of our knowledge, to date there are no studies carried out with post-COVID-19 patients that evaluate a similar intervention with a clinical trial methodology. We will use the difference pre-post score of the short-form 36-item questionnaire (SF-36), the value of the possible highest standard deviation (SD), and a minimum expected difference of 19.3 points in the pre-post rating, which were all taken into account. Accepting a risk alpha of 0.05 and a power of 95% in a bilateral contrast, 70 subjects would be required. A maximum loss-to-follow-up rate of 10% has been estimated. The total sample required is 78 subjects, distributed between the two groups (control–intervention).

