#### 2.2.7. Variables and Instruments

An evaluation will be carried out at baseline with further assessments three and six months following the end of the intervention. The assessors administering the instruments will be blind to the type of treatment given to the patients. Patients will be contacted by phone at six weeks to monitor their adherence to APP recommendations and exercises in the intervention group and important changes in their health (e.g., reinfection) or treatment in both the control and intervention groups. 

The main variable will be quality of life, assessed by the SF-36 Questionnaire [67], which measures eight dimensions of health: physical function, physical role, aches and pains, general health, vitality, social function, emotional role, and mental health. In addition, it incorporates a declared health progress item. The eight dimensions define two main components of health: physical summary component and mental summary component, where scores above or below 50 indicate better or worse health status, respectively, than the mean of the reference population. The items are scored on Likert-type scales ranging from 1 to 3.5 or 6 depending on the type of item. The eight scales are scored from 0 to 100, with higher scores indicating better health status. The official Spanish version of the questionnaire [68] will be used.

Secondary results: The following variables will be collected

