
#### 2.2.8. Statistical Analysis 

Analysis of the outcomes at baseline consist of the following measures. First, descriptive analysis of all of the variables (frequencies for categorical variables; means and standard deviation for continuous variables) will be carried out. A univariate analysis (one-way ANOVA and chi-square) will be used to examine the data and test whether there are baseline differences between groups after randomisation.

Statistical analyses will be chosen based on the sub-sample size (parametric or non-parametric tests). Data collection and statistical analyses will be performed using Excel software, SPSS software (version 25.0) [117], and the R statistical software environment (version 3.6.2) [118]. 

Clinical effectiveness analysis: The report of the results will follow a pre-specified plan based on CONSORT guidelines [119] in order to compare the two groups. Initially, a descriptive comparison (proportions, means, or medians) will be carried out between groups for prognostic variables in order to establish their baseline comparability after randomisation. To analyse the clinical effectiveness, a repeated-measure linear regression will be conducted, including all evaluations over time. For this purpose, the main variable, SF-36 score, will be used as a continuous variable. The models will include adjustments for the baseline value of the SF-36 and for any other variable that would show differences in the baseline measurement. Possible group per time interactions will be examined using linear regression. Similar analyses will be carried out using the secondary outcomes (number and severity of persistent symptoms, Montreal Cognitive Assessment, Sit-to-Stand Test, and HAD test). To counteract the problem of multiple comparisons we will use Bonferroni correction.

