Cost-efficiency and cost-utility analysis are as follows. The effectiveness of the interventions will be estimated using the difference between the SF-36 score at the baseline and at the three and six-month follow-up, and the utility will be estimated using QALYs at the three and six-month follow-up. QALYs will be calculated based on these scores using the Spanish EQ-5D tariffs [120]. Along with the number and severity of the ongoing symptoms, scores will also be used as an outcome for the analysis. Cost-efficiency will be explored through the calculation of incremental cost-efficiency ratios (ICERs) for the intervention group using the TAU group as the control. ICER is defined as the ratio between incremental costs and incremental effectiveness. In the same way, cost utility will be explored through the calculation of incremental cost-utility ratios (ICURs), which are defined as the ratio between incremental costs and incremental utilities measured on QALYs. QALYs gained in each evaluation are approximated by using the area under-the-curve technique [121]. Total costs will be calculated by adding direct and indirect costs. Direct costs will be calculated by adding the costs derived from the medication and the use of health services and clinical tests. The medication costs will be calculated by determining the price per milligram during the study period according to the Vademecum during the last year of the study, including value-added tax (VAT). The total cost of drug treatment will be calculated by multiplying the price per milligram by the daily dose in milligrams and the number of days the treatment is received. Costs derived from the use of health services will be calculated considering the data from the Oblikue database [122]. Indirect costs will be calculated based on the number of days taken on sick-leave and multiplying them by the Spanish minimum daily wage during the study period 2019–2020. We assume that data will be missing at random (MAR). Only patients with both cost and relevant outcome data at three and six-month follow-up will be included in the cost-efficiency and cost-utility analyses. Notwithstanding, sensitivity analysis imputing missing three and six-month data will test the robustness of the cost-efficiency and cost-utility results. The imputations will be performed using the package “mice” [123], freely available in cran-R [118].

Variables collected, instruments, and measures are shown in Table 1. 

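### The economic analysis takes SF-36 effectiveness as change from baseline and QALYs as area under the curve and states no baseline adjustment for either, although the clinical analysis adjusts the same SF-36 score

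*Protocol article*

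**What the plan says.** All the relevant text is in section 2.2.8 of the protocol article.

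- **Clinical effectiveness.** A repeated-measures regression of SF-36 is planned, and "The models will include adjustments for the baseline value of the SF-36". Variables that differ between arms at baseline are also to be adjusted for.
- **ICER.** Effectiveness is "estimated using the difference between the SF-36 score at the baseline and at the three and six-month follow-up". The ratio itself is defined generically: "ICER is defined as the ratio between incremental costs and incremental effectiveness".
- **ICUR.** "QALYs gained in each evaluation are approximated by using the area under-the-curve technique", and the ICUR is "the ratio between incremental costs and incremental utilities measured on QALYs".
- **Analysis set.** "Only patients with both cost and relevant outcome data at three and six-month follow-up will be included" in the economic analyses. Multiple imputation is a sensitivity analysis.

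The economic paragraph is detailed on drug prices, VAT, sick-leave costs and the imputation package. It names no baseline covariate and no regression for the incremental effect or the incremental QALYs.

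**The concern.** The same SF-36 score is handled in two ways within one section: with baseline as a covariate for the clinical result, and as a change from baseline for the ICER denominator. Read at face value, the report could carry two treatment effects for one outcome, and the less precise one would feed the economic result.

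For QALYs, baseline utility enters the area under the curve directly and is also correlated with the later utilities. If arms are compared without a baseline term, a chance difference in starting utility shows up as part of the QALY difference.

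Cost-efficiency is part of the trial's stated objective, and the arms are small. What is at stake is the precision of the ICER and ICUR denominators and how much they depend on a chance imbalance.

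**Working it through.** **Inputs from the documents.** Section 2.2.3 states: "Accepting a risk alpha of 0.05 and a power of 95% in a bilateral contrast, 70 subjects would be required". With 10% loss, 70 / 0.9 = 77.8, which reproduces the stated total of 78. The allocation ratio is not given, so I assume 1:1, or 35 evaluable per arm. Section 2.2.7 states: "An evaluation will be carried out at baseline with further assessments three and six months following the end of the intervention". I treat the visits as 0, 0.25 and 0.5 years.

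**Assumptions not in the documents.** The correlation rho between any two visits is 0.3 to 0.8, SDs are equal across visits, and the utility SD is 0.15 to 0.25.

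**Size of chance imbalance.** The standard error of a baseline difference is SD × √(2/35) = 0.239 SD.
- Utility SD 0.25: SE = 0.060, so P(|difference| ≥ 0.05) ≈ 0.40.
- Utility SD 0.15: SE = 0.036, so the same probability is ≈ 0.16.

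**SF-36 change score.** Given a baseline difference d, the change-score comparison is off by (rho − 1) × d. It over-corrects, against the arm that starts higher. The variance relative to a baseline-adjusted comparison is 2(1 − rho) / (1 − rho²) = 2 / (1 + rho).

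**Total area under the curve.** QALY = 0.125·u0 + 0.25·u3 + 0.125·u6.
- Carry-over per unit of baseline utility difference: c = 0.125 + 0.375·rho. It under-corrects, in favour of the arm that starts higher.
- In units of the utility variance, Var = 0.09375 + 0.15625·rho, and the adjusted variance is Var − c².
- Example at rho = 0.3: Var = 0.1406, c² = 0.0564, ratio = 0.1406 / 0.0842 = 1.67, SE ratio = 1.29.

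**Area above baseline** (the other reading of the word gained). The weights become −0.375, 0.25 and 0.125. The carry-over is −0.375·(1 − rho), and the variance is 0.21875·(1 − rho).

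SE ratios below are unadjusted over adjusted.

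| rho | SF-36 change: carry-over | SF-36 change: SE ratio | Total area: carry-over | Total area: SE ratio | Above baseline: carry-over | Above baseline: SE ratio |
|---|---|---|---|---|---|---|
| 0.3 | −0.70 | 1.24 | 0.24 | 1.29 | −0.26 | 1.35 |
| 0.5 | −0.50 | 1.15 | 0.31 | 1.52 | −0.19 | 1.21 |
| 0.7 | −0.30 | 1.08 | 0.39 | 1.96 | −0.11 | 1.11 |
| 0.8 | −0.20 | 1.05 | 0.43 | 2.40 | −0.08 | 1.07 |

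A baseline utility difference of 0.05 therefore moves incremental QALYs with no treatment effect at all. On the total-area reading the shift is 0.05 × 0.2375 = 0.012 (rho 0.3) to 0.05 × 0.425 = 0.021 (rho 0.8). On the above-baseline reading it is −0.013 to −0.004. The two readings have equal size at rho = 1/3. Above that, the above-baseline reading gives the smaller carry-over and the smaller loss of precision.

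**The case against.** The strongest reply is that the text nowhere says QALYs will be left unadjusted. Area under the curve describes how each patient's QALYs are built, not how the arms are compared, and a ratio of increments is compatible with adjusted increments. The article condenses a fuller plan, which may name the covariates. This stands: for QALYs, the lack of adjustment is inferred from silence. For SF-36 the reply is weaker, because the article names a change from baseline and does not carry over the adjustment stated for the clinical model. A change score with baseline as a covariate would give the same treatment effect as the clinical approach, but the article does not say that this is meant.

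A reader might also infer four stronger things that the documents do not support.

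- **That the economic estimates are biased.** Under randomisation both comparisons are unbiased on average; the error is conditional on the observed imbalance. The complete-case restriction may disturb the balance that randomisation gives, but no figure in the documents sizes this.
- **That baseline imbalance passes straight into both ratios.** It does not for SF-36. The change score already subtracts baseline and errs in the opposite direction, with a modest loss of precision.
- **That a material imbalance is likely and could reverse the ICUR.** An imbalance of 0.05 or more is less likely than not across the assumed range, and the documents give no expected QALY difference to compare it with.
- **That baseline utility is already in hand.** EQ-5D tariffs are applied, but neither section 2.2.7 nor Table 1 lists an EQ-5D instrument.

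**Conclusion.** The point holds as a matter of precision and conditional error, and not as a claim of bias. The economic paragraph specifies a change score and area-under-the-curve QALYs and states no baseline adjustment, while the clinical paragraph adjusts the same score.

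The cost is modest for SF-36 and can be large for QALYs on the total-area reading. If utility and SF-36 are unbalanced in the same direction, the change score and the total area err in opposite directions, so one imbalance could pull the ICER and ICUR denominators apart. The article does not settle which area is meant.

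All sizes rest on the assumed correlations, equal SDs, the assumed utility SD and 35 per arm. It is worth changing because a better method is available at little cost.

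**What to change.** - Take the incremental SF-36 effect in the ICER from the baseline-adjusted model already specified for clinical effectiveness, so that one outcome has one effect estimate.
- State that incremental QALYs are estimated by regressing QALYs on arm and baseline utility, and use the adjusted difference in the ICUR. With baseline utility in the model, total area and area above baseline give the same arm difference, so that ambiguity no longer matters for the comparison.
- First settle the source of the utilities. Baseline utility must be derived from the same source as the follow-up utilities.

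The cost is a few sentences and one further regression. Baseline SF-36 is already collected. Whether baseline utility is available depends on how its source is settled. Section 3 reports recruitment still being completed, with 60 patients randomised, so at that point the change could be made before the analysis.

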-Physical activity will be measured using the International Physical Activity Questionnaire-Short Form (IPAQ-SF) [103]. It assesses the levels of habitual physical activity over the preceding seven days. It has seven items and records activity at four levels of intensity: vigorous-intensity activity and moderate-intensity activity (walking and sitting). We will use the official Spanish version [104]. IPAQ-SF has sufficient validity for the measurement of total and vigorous physical activity and poor validity for moderate activity and good reliability [105].-Adherence to a Mediterranean diet will be measured using the 14-item Mediterranean Diet Adherence Screener (MEDAS), encouraging compliance to a Mediterranean diet [106]. It includes items on food consumption and intake habits. The total score ranges from 0 to 14, with a higher score indicating greater adherence to the Mediterranean diet [107].-Personal constructs. The personal factors relating to behaviour that will be collected are the following:(a)Self-efficacy will be measured using the Self-Efficacy Scale-12 [108]. The original scale consisted of 17 items that are scored on a 5-point Likert scale. Woodruff and Cashman [109] obtained a factor structure, based on the original 17-item scale, that represented the three aspects underlying the scale, i.e., willingness to initiate behavior, `Initiative’, willingness to expend effort in completing the behavior, `Effort’, and persistence in the face of adversity, `Persistence’. Five items were excluded because of low item-rest correlations and ambiguous wording, resulting in a 12-item version of the scale (GSES-12). This scale has 3 factors: Initiative (willingness to initiate behavior), Effort (willingness to make an effort to complete the behavior), and Persistence (persevering to complete the task in the face of adversity). Internal consistency of the original scale was 0.64 for initiative, 0.63 for effort, and 0.64 for persistence. The total scale obtained a Cronbach’s Alpha coefficient of 0.69 [110].(b)Patient activation in their own health will be measured using the Patient Activation Measure (PAM) questionnaire with regard to the management of their health [111]. It evaluates the patient’s perceived knowledge, skills, and confidence to engage in self-management activities through 13 items with a Likert Scale from one (strongly disagree) to four (strongly agree). The resulting score ranges between 13 and 52. Higher scores indicate higher levels of activation. There is only an official Spanish version for chronically ill patients. It has an item separation index for the parameters of 6.64 and a reliability of 0.98 [112].(c)Health literacy will be measured using the Health Literacy Europe Questionnaire (HLS-EUQ16) [113]. Health literacy is defined as the knowledge of the population, their motivation, and their individual ability to understand and make decisions related to the promotion and maintenance of their health. The questionnaire consists of 16 items, scored between 1 (very easy) and 4 (very difficult). The score of each subject was obtained as the sum of the scores of the 16 items. The final score can be transformed into a dichotomous response: very difficult and difficult = 0, as well as easy and very easy = 1. Higher scores indicate worse health literacy. It presents a high consistency (Cronbach’s alpha of 0.982) in the official Spanish version [114].-For the analysis of the cost-efficiency, the Client Service Receipt Inventory will be used [115], collecting information on the entire range of services and support used by study participants. It retrospectively collects data on the use of services over the preceding six months (e.g., rates of use of individual services, mean intensity of service use, rates of accommodation use over time). We will use the official Spanish version [116].

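### The QALY rule applies EQ-5D tariffs to SF-36 scores, with no EQ-5D listed and no conversion stated, so the cost-utility analysis cannot be carried out as written

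*Protocol article*

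**What the plan says.** Section 2.2.7 makes the SF-36 the primary outcome: "The main variable will be quality of life, assessed by the SF-36 Questionnaire". It describes the output as eight scales and two summary components: "The eight scales are scored from 0 to 100, with higher scores indicating better health status". For the economic part it names one instrument: "For the analysis of the cost-efficiency, the Client Service Receipt Inventory will be used". That inventory records service use.

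Section 2.2.8 then sets out the economic analysis:

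- Effectiveness: "The effectiveness of the interventions will be estimated using the difference between the SF-36 score at the baseline and at the three and six-month follow-up".
- Utility: "the utility will be estimated using QALYs at the three and six-month follow-up".
- Source of the QALYs: "QALYs will be calculated based on these scores using the Spanish EQ-5D tariffs".
- Construction: "QALYs gained in each evaluation are approximated by using the area under-the-curve technique".

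The incremental cost-utility ratio (ICUR) divides incremental cost by incremental QALYs. The separate incremental cost-efficiency ratio (ICER) divides incremental cost by incremental effectiveness.

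**The concern.** The tariff and the instrument do not match. An EQ-5D tariff takes as input a health state described on the five EQ-5D dimensions and returns a utility. SF-36 scales running from 0 to 100, or summary components referenced to 50, are not such states, and the tariff holds no entry for them.

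If the sentence stays, whoever analyses the data must choose a route from SF-36 to utilities that the plan does not state: SF-6D, some mapping function, or another device. Different routes can give different utilities. The ICUR would then rest on a choice that may be made after the outcome data have been seen.

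**Working it through.** No arithmetic in the plan needs reproducing. The check is whether the stated inputs can feed the stated rule.

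**1. Which scores are meant.** The sentence before the tariff rule names one score only, the SF-36 at baseline and at the two follow-ups. The sentence after it mentions symptom number and severity and then refers to scores without naming an instrument, so it supplies no other candidate.

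**2. What the calculation needs.** With utilities u0, u1 and u2 at baseline and the two follow-ups, and elapsed times t1 and t2, the area-under-the-curve method gives for each patient

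QALY = t1 × (u0 + u1)/2 + (t2 − t1) × (u1 + u2)/2.

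All three utilities are needed. Then

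ICUR = (mean cost in the intervention arm − mean cost in the control arm) / (mean QALY in the intervention arm − mean QALY in the control arm).

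If u0, u1 and u2 are undefined, so are the QALYs and the ICUR.

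**3. What the listed instruments supply.**

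| Candidate source | Where listed | What it gives | Valid input to an EQ-5D tariff? |
|---|---|---|---|
| SF-36 | 2.2.7, Table 1 | Eight 0–100 scales, two summary components | No, not directly |
| Client Service Receipt Inventory | 2.2.7, Table 1 | Service use | No |
| Visual analogue scale | 2.2.7, Table 1 | Severity of residual symptoms | No; not described as part of EQ-5D |
| EQ-5D | Not listed | – | Would be, if collected |

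Table 1 has a single quality-of-life row, and it contains only the SF-36. EQ-5D occurs once in the article, in the tariff sentence. SF-6D and a mapping algorithm do not occur at all.

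**4. What depends on the step.** The ICER uses change in the SF-36 itself and needs no utility. The repeated-measures analysis of the SF-36 needs none either. The damage is confined to the QALYs and the ICUR, but there it covers both arms and every visit.

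**5. Timing.** Section 3 reports 60 patients assessed and randomised, and Section 2.2.5 places baseline data collection before randomisation. The planned total in Section 2.2.3 is 78. If EQ-5D was not administered, the share of the planned sample whose baseline EQ-5D can no longer be obtained is 60/78 = 77%.

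**The case against.** Four points can be made for the plan.

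*EQ-5D may be administered and simply not listed.* This is possible. A reader might infer from the instrument list that the trial never collects EQ-5D. The article shows only that it is not listed. Even so, Section 2.2.8 presents Table 1 as the list of variables and instruments, so under this reading Section 2.2.7, Table 1 and the reference to the SF-36 scores all need correcting.

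*A mapping may be intended.* Converting SF-36 responses to EQ-5D and valuing the result with a Spanish tariff would be a legitimate way to reach QALYs. It would therefore be too strong to say that the SF-36 data cannot yield EQ-5D-based utilities. But the text speaks of tariffs and names no mapping. The content of the cited tariff source is not shown. The supportable statement is that the tariff cannot be applied directly to SF-36 scores and that the connecting step is not stated.

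*An article condenses, and an analysis plan may hold the detail.* That would excuse silence. Here the article states a specific rule that conflicts with its own instrument list, and an analysis plan that followed the rule would inherit the conflict.

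*The consequence is limited.* This stands. A reader might infer that half of the study objective is lost, because cost-efficiency appears in it beside effectiveness. The documents do not support that. The objective in the Abstract and Introduction names cost-efficiency, which Section 2.2.8 measures by the SF-36-based ICER. Cost-utility is a separate analysis in the same section.

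**Conclusion.** The concern holds for the cost-utility analysis. As written, the QALYs and the ICUR have no usable input in either arm at any visit. The primary outcome, its analysis, the sample size and the SF-36-based ICER are untouched.

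The conclusion rests on two readings: that the back-reference in the tariff sentence points to the SF-36, the only score named, and that Section 2.2.7 and Table 1 together are the full instrument list, as the article presents them. If the second reading is wrong and EQ-5D is collected, the analysis is feasible and the error is one of documentation.

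The figure of 60 of 78 patients without an obtainable baseline EQ-5D is conditional. It applies only if EQ-5D was not administered, and it matters only if EQ-5D were chosen as the remedy. A route through the SF-36 loses no data on this account.

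**What to change.** First establish whether EQ-5D is administered. Then, before outcome data are analysed:

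- **If it is not,** replace the tariff sentence with a derivation that the collected data support. For example: utilities will be derived from SF-36 item responses at baseline and at the three- and six-month follow-ups with the SF-6D algorithm and a named value set, and QALYs will be the area under the resulting utility curve. A named, validated mapping from SF-36 to EQ-5D, valued with the Spanish tariff, is an acceptable alternative. Which of the two is primary is for the study team to decide, provided that one is fixed in advance. With baseline EQ-5D out of reach for the 60 patients already randomised, a route through the SF-36 is the practical one.
- **If it is,** add EQ-5D to Section 2.2.7 and Table 1 with its version and visits, and correct the tariff sentence so that it refers to EQ-5D responses and not to the SF-36.

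The cost is a revised sentence and a scoring script, or an entry in the instrument list. The SF-36 route assumes that responses are held at item level. It then needs no further data collection and adds no burden for patients.

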#### 2.2.6. Intervention

1st Recommended treatment (TAU) prescribed by health care professionals in accordance with NICE Guidelines and CAMFiC’s Manifestaciones persistentes de la COVID-19: Guía de práctica clínica [Ongoing manifestations of COVID-19: Clinical Practice Guidelines] and its subsequent updates.

2nd TAU plus the use of the APP as a community resource + three face-to-face motivational interviewing sessions to increase adherence. 

The content of the APP is based on scientific evidence that aims to alleviate the symptoms of patients diagnosed with long COVID-19 [48,49,50,51,52]. Depending on their health status, the participants will find all the advises useful, or only those that respond to their health needs based on the persistent symptoms they present will be helpful. However, it is emphasized that, if they cannot carry out any of the recommendations or exercises, or it causes them any type of discomfort, they should stop doing them immediately. The information provided in the APP has been divided into six work areas: (1) recommendations for following the Mediterranean diet; (2) recommendations for improving the sleep quality; (3) physical exercise recommendations with visual aids (i.e., charts); (4) respiratory physiotherapy exercises supported by video tutorials; (5) cognitive stimulation exercises with different levels of difficulty and (6) use of community resources. There is an additional section on behavioral activation and evidence-based documentation on managing long COVID-19. In all these sections, self-assessments and records are provided to record their activity so that patients can graphically observe their evolution over time as they continue to use the APP.

The content and operation of each of each section is detailed below:Diet

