In addition to the use of the APP, the intervention group will attend three face-to-face sessions held over three consecutive weeks with the aim of encouraging adherence to the APP, based on a motivational interview (MI). The first and second sessions will be individual, and the third will be a group session. All of them will be conducted by two study researchers with training to standardise the intervention, as well as with specific training, to carry out these sessions in accordance with Miller and Rollnick’s guidelines [62]. MIs will be conducted for 20–30 min, in alignment with the health belief model, which identifies the link between treatment adherence and health behavior [63,64,65].

This way of working follows Miller and Rollnick’s [62] definition of MI, which is “A collaborative, goal-oriented style of communication with particular attention to the language of change. It is designed to strengthen personal motivation for and commitment to a specific goal by eliciting and exploring the person’s own reasons for change within an atmosphere of acceptance and compassion”. Thus, MI is an interviewing method centred around the patient, which aims to evoke behavioural change by helping patients to understand and solve their problems [66]. Additionally, in the first session, the APP will be installed, and the participant will be taught how to manage and use it. The second session will be focused on sharing experiences of the first week of using the APP, addressing technological and content concerns, and setting goals they want to achieve through its use. The third session will be in groups (around 10–15 participants in each group) and will last for approximately one hour. In this last session, the benefits of using the APP and other community HAs as an adjuvant treatment will be discussed. 

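### The cost definition has no term for delivering the APP and the three motivational sessions, so incremental cost is understated by the delivery cost per participant

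*Protocol article*

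**What the plan says.** Section 2.2.8 of the protocol article states the cost rule in three sentences:

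- Direct part: "Direct costs will be calculated by adding the costs derived from the medication and the use of health services and clinical tests".
- Indirect part: "Indirect costs will be calculated based on the number of days taken on sick-leave", multiplied by the minimum daily wage.
- Sum of the two parts: "Total costs will be calculated by adding direct and indirect costs".

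Price sources follow. Drugs are priced per milligram from the Vademecum including VAT, and for services "Costs derived from the use of health services will be calculated considering the data from the Oblikue database". No price source is named for the APP or for the motivational sessions.

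These costs enter the "incremental cost-efficiency ratios (ICERs) for the intervention group using the TAU group as the control", where "ICER is defined as the ratio between incremental costs and incremental effectiveness". The cost-utility ratio has the same numerator, divided by incremental QALYs.

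Section 2.2.6 describes the experimental arm as "TAU plus the use of the APP as a community resource + three face-to-face motivational interviewing sessions to increase adherence". On staffing of the sessions it says: "All of them will be conducted by two study researchers with training to standardise the intervention". Section 2.1.3 adds that the APP's self-assessment data sit on a cloud-hosted database.

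**The concern.** An incremental ratio of the intervention against usual care should carry, in its numerator, what it costs to provide the intervention. Here the listed components cover what may change downstream (drugs, service use, tests, sick leave) but not the thing being provided. The omission works in one direction only: it lowers incremental cost.

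This bears on a stated aim. The Abstract and Introduction put cost-efficiency beside effectiveness in the study objective, and Section 2.1.5 gives offering the APP to the whole community as the ultimate goal. A decision on wider provision needs the cost of provision in the ratio. The only sensitivity analysis described for the economic results concerns imputation of missing data, so it would not reveal the gap.

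**Working it through.** The article gives no cost or ratio to reproduce. The check therefore sets the cost definition against the intervention's resources and then sizes what is left out.

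**1. Does any cost component cover delivery?**

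| Resource that differs between arms | Where described | Component in 2.2.8 that names it |
|---|---|---|
| Two individual sessions and one group session, run by study researchers | 2.2.6 | None |
| APP installation and instruction | 2.2.6, within the first session | None (part of session time) |
| APP hosting and maintenance | 2.1.3 (hosting described; maintenance implied by running an APP) | None |

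The six-week telephone contact in Section 2.2.7 goes to both arms, so it is not a planned difference between them.

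**2. Effect on the ratios.** Let ΔC be incremental cost under the stated definition, c the delivery cost per intervention participant, ΔE the incremental effect and ΔQ the incremental QALYs.

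- Incremental cost with delivery included: ΔC + c.
- Shift in the cost-efficiency ratio: (ΔC + c)/ΔE − ΔC/ΔE = c/ΔE.
- Shift in the cost-utility ratio: c/ΔQ.

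Both shifts make the stated ratio too favourable when the effect is positive.

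**3. Staff time from the article's own figures (2.2.6).** The inputs are two individual sessions, taken here at 20–30 minutes each, and one group session of about 60 minutes shared by 10–15 participants. Minutes per participant = 2 × individual minutes + 60 / group size.

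- Low: 2 × 20 + 60/15 = 44 minutes.
- High: 2 × 30 + 60/10 = 66 minutes.
- If both researchers attend every session: 88–132 minutes.

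The article does not say whether both attend each session, so both cases are shown. If the 78 participants are split equally (the ratio is not stated), 39 in the intervention arm means 28.6–42.9 hours with one facilitator or 57.2–85.8 hours with two.

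**4. In euros, under assumptions.** None of the following unit values is in the documents.

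- Staff cost of EUR 20–60 per hour: 20 × 44/60 ≈ EUR 15, up to 60 × 132/60 = EUR 132 per participant.
- QALY gain of 0.01–0.05: 15/0.05 = EUR 300, up to 132/0.01 = EUR 13,200 per QALY.
- With a further assumed APP cost of EUR 100–300 per participant: (15 + 100)/0.05 = EUR 2,300, up to (132 + 300)/0.01 = EUR 43,200 per QALY.

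**The case against.** The strongest reply is that the cost rule does not say these components are the only ones, and does not exclude the sessions from use of health services. Section 2.2.7 describes the Client Service Receipt Inventory as covering all services and support that participants use, so a participant could report the sessions there. The article also covers the economics in one paragraph, and itemised unit costs, perspective and treatment of development cost often belong in a fuller plan.

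Part of this stands. Some session cost could enter through the inventory, so it cannot be said that every euro of delivery is certain to be left out. Three points limit the reply:

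- Nothing in the article provides for that route. It would depend on whether participants report researcher-led sessions as services and whether analysts then find a price for them.
- The inventory looks back six months. Sessions could fall inside that window at the three-month assessment. At the assessment six months after the end of the intervention they lie at or beyond its edge.
- It could not cover APP hosting or maintenance.

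The level-of-detail argument is weaker. The paragraph goes down to price per milligram, VAT and the wage used, and it states the sum and its parts. The concern is with a stated sum that lacks a term, not with a missing unit-cost table.

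A reader might also infer that the omission would turn a costly result into a cost-saving one. That happens only if the true incremental cost is positive and smaller than the omitted amount, and the document gives no basis for expecting it.

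**Conclusion.** The point holds. As written, the cost definition has no term for delivering the intervention, and incremental cost is understated by whatever part of c does not enter by another route. At most that is the whole of c. The direction follows from the definition. The staff time of 44–132 minutes per participant follows from Section 2.2.6, with 20–30 minutes taken for the individual sessions. The euro and per-QALY figures rest entirely on assumed hourly rates, APP cost and QALY gain, and indicate scale only. The ratio shifts also assume a positive incremental effect.

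It would go too far to say that the plan treats the whole intervention as free. Downstream effects on medication, service use, tests and sick leave are counted; the gap concerns delivery only. The primary SF-36 comparison, the randomisation and the sample size are untouched.

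**What to change.** Add a sentence to the cost paragraph of Section 2.2.8, for example: *Direct costs in the intervention arm also include the cost of delivering the intervention, namely staff time for the three motivational sessions, valued at a named unit-cost source, and APP hosting and maintenance per user.*

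Then settle four details:

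- Compute staff time from the planned durations and group size, or from recorded attendance if it exists (the article mentions no session records), and state whether one or two researchers are costed per session.
- Do not cost installation separately, since it takes place within the first session.
- Exclude these sessions from service costs derived from the inventory, so that they are not counted twice.
- Show APP development cost separately in a sensitivity analysis.

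The cost of the change is a small costing table and less favourable ratios. It requires no new patient data and no change to the trial's conduct.
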